#### VHT distribution channel

Uganda’s national community health worker program is organized as VHTs who serve as a HH’s first point of contact for various health-related issues. Working primarily as volunteers, VHTs are ordinary community members who receive basic health care training to provide home visits and health management services. CRS will recruit approximately 32 VHTs to distribute SR, collect and dispose of old SR, and provide HH-level education about SRs. VHTs will be recruited from the existing VHT pool, which was identified and trained by the MOH. Lists of active VHTs are available at the health facilities and with the health cluster lead agency. All the VHTs in the refugee settlement have experience implementing integrated Community Case Management (iCCM) for childhood illness and the provision of other interventions such as ITN, immunization, and health education. Once recruited, the VHTs will receive additional training with regards to study procedures around the SR product itself, how to hang, remove, and safely dispose of it, as well as documenting and monitoring the process. VHTs recruited for study activities will also receive a remuneration for their activities based on locally approved rates.

Upon enrollment into the study, HH participating in clusters assigned to the VHT distribution channel will be visited monthly by a trained VHT. During the home visit, the VHT will distribute the appropriate number of SRs based on measurements for all structures in the HH. They will also retrieve used SR and dispose appropriately. The VHTs will track distribution and retrieval and follow-up on discrepancies as needed to ensure safe product disposal according to the manufacturer’s instructions. During the home visits, VHTs will share key educational information about malaria prevention, the SR, including appropriate placement on the walls, safety, side effects, etc. The study team will check to see if the SRs are hung appropriately and address any issues with the residents. VHTs will address any questions or concerns the participating HH might have.

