Along with many other multilateral and international organizations, Catholic Relief Services (CRS) provides humanitarian assistance to victims of natural and man-made emergencies across the world, including three longstanding conflicts in Uganda. Because of the high burden of malaria and the history of CRS’ efforts in this region, the site was selected to evaluate the effectiveness of a new SR product formulated to last up to 1 month for the prevention of malaria using a cluster randomized control trial (cRCT) study design. The study will enroll children 6 months to 59 months of age as study participants into three separate cohorts and followed to determine the time to first malaria infection with monthly RDTs. The study will include separate cohorts to measure the direct effect of SRs as well as the protection to participants using varied distribution channels: paid study personnel (reference arm-positive control), Village Health Teams (VHTs), and a voucher system. The voucher system will be modeled based on CRS’ past experience using vouchers in bed net distributions and emergency response programs.

This evaluation will serve as an effectiveness trial of SR products for sub-Saharan Africa emergency response and recovery contexts. Evidence will inform health impact and equivalence of impact through different ‘real-life’ delivery systems for donor market introduction. The cRCT will evaluate operational effectiveness against malaria infections in a rural African environment linked to displaced persons where ITNs and indoor residual spraying (IRS) may be constrained. Findings and operational use guidance will be submitted to the World Health Organization (WHO), in coordination with the Ministry of Health (MOH) in Uganda.

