### Objectives {7}

The primary objective of the study is to demonstrate and quantify the effectiveness of a SR product, in reducing malaria infection in human cohorts under operational program conditions. The design will be a prospective cRCT representing an operational research study.

To compare the effectiveness of SR against malaria infection (both first-time and recurrent) between each of the two operational program delivery mechanisms (1. VHTs delivering SR directly to participants (VHT); 2. participants redeeming a voucher for SR at a central location and applying it in structures themselves (Voucher)) vs a reference distribution channel (positive control; study team personnel delivering product directly to participants at their homes).

Secondary objectives are (1) to estimate the cost-effectiveness of SR distribution by each distribution channel (VHT and Voucher) compared to the reference distribution channel, and (2) assess the safety of the SR product.

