#### Study personnel distribution channel (reference arm)

In the reference arm, the SR products will be delivered and replaced by paid study personnel throughout the intervention period. The study personnel will distribute the SR every month during a data collection home visit. They will also retrieve used SR to ensure proper disposal of SR. Study personnel will track distribution and retrieval and follow-up on any discrepancies as needed to ensure safe product disposal.

CRS study staff will be employed to ensure proper storage of unused products at site and supply management and coordination for the timely replacement of products in the reference arm. The CRS study team will also perform periodic, unannounced spot checks in a random 10% of enrolled HHs during intervention to monitor SR product compliance (installation according to manufacturer specifications) and ITN usage, if available.

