### Strategies to improve adherence to interventions {11c}

In order to promote adherence to intervention protocols, standard operating procedures will be developed for clinical tests, drug administration, distribution modalities, and all other study processes. Study staff will be employed and trained to ensure the timely replacement and accurate placement of the SR products. Additionally, they will perform periodic, unannounced spot checks to confirm the SR product is properly installed. If study staff observe a product has been moved after application during a scheduled product replacement, the move will be recorded for use in HH compliance assessment. If necessary, study staff will re-engage with heads of HHs on the importance of maintaining original product placement. Overall product coverage will be estimated based on total HHs recorded having product volume at time of replacement according to manufacturer specifications (2 units/9 m^2^).

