### Implementation {16c}

Trained study staff will be responsible for the management of product implementation which will include the initial deployment of product, subsequent removal, and replacement at 4-week intervals.

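### Study staff check and correct repellent placement in the VHT arm, which may pull that hazard ratio toward 1; the wording leaves the voucher arm unclear

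*Protocol article*

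**What the plan says.** The protocol article's Objectives {7} set out to measure the SR's effect "in reducing malaria infection in human cohorts under operational program conditions". The two operational channels are defined by who delivers and places the product. The voucher channel is "participants redeeming a voucher for SR at a central location and applying it in structures themselves"; in the VHT channel the VHTs deliver it. The Background section adds a use for the result: "Evidence will inform health impact and equivalence of impact through different" delivery systems.

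The section on the VHT distribution channel then gives a task to a different group: "The study team will check to see if the SRs are hung appropriately and address any issues with the residents". The sentences around it name the VHTs separately, so the study team is not the VHTs. How often this happens, and in what share of homes, is not stated.

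Two general sections name no arm:
- Strategies to improve adherence {11c} employs study staff to see that product is replaced on time and placed correctly. If needed, "study staff will re-engage with heads of HHs on the importance of maintaining original product placement".
- Implementation {16c} says: "Trained study staff will be responsible for the management of product implementation which will include the initial deployment of product, subsequent removal, and replacement" every 4 weeks.

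Under the reference-arm heading, staff also make "periodic, unannounced spot checks in a random 10% of enrolled HHs during intervention to monitor SR product compliance".

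**The concern.** Correct hanging is one of the ways in which delivery by VHTs or by the household itself can fall short of delivery by paid staff. If research staff find and put right poor hanging in VHT homes, part of the reference condition is applied to a comparator. Where VHT placement is the worse of the two, the VHT HR moves toward 1, the value that would be read as equal impact. Checks in the reference arm do not cancel this, because product installed by staff leaves less to repair.

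The cost-effectiveness comparison is exposed in the same way. Protection gained through research supervision may be credited to the VHT channel, and the article does not say that the cost of that supervision is charged to it.

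**Working it through.** **1. The plan's own precision figure.** Inputs from Sample size {14}: 16 clusters per arm, 40 households per cluster, between-cluster coefficient of variation 0.40, 12 months, 10% loss, 0.5 to 1 infection per person-year. The 90% interval is from Statistical methods {20a}.

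Expected first infections per cluster: e = 40 × 0.9 × (1 − exp(−rate)).
SE(log HR) = √[(2/16)(1/e + 0.40²)]; bounds = exp(±1.645 × SE).

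- Rate 1.0: e = 22.8, SE = 0.1597, bounds 0.769 to 1.300.
- Rate 0.5: e = 14.2, SE = 0.1698, bounds 0.756 to 1.322.

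The stated bounds are 0.77 to 1.30 and 0.75 to 1.33, so they are reproduced within 0.01.

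**2. What the text gives study staff to do, by arm.**

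| Arm | Arm-specific text | Correction of placement by study staff |
|---|---|---|
| Reference | Staff deliver, replace and spot-check | Part of the channel |
| VHT | VHTs deliver and retrieve; study team checks hanging and deals with problems | Explicit, extent not stated |
| Voucher | Staff supply product and placement training in month 1; households redeem for 11 months, with reminders | None described after month 1; only the arm-neutral text of {11c} and {16c} could imply it |

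**3. Possible size.** The article has no figure for this, so every input here is assumed. Let E be SR protection, c the share of time correctly covered in the operational arm without staff help, 0.95 the same share in the reference arm, and r the share of the shortfall that staff repair. With incidence proportional to 1 − E × coverage:

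HR = [1 − E × (c + r(0.95 − c))] / [1 − 0.95E].

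E = 0.30 and c = 0.60 give a denominator of 0.715:
- r = 0: 0.82/0.715 = 1.147
- r = 0.10: 0.8095/0.715 = 1.132
- r = 0.25: 0.79375/0.715 = 1.110
- r = 0.50: 0.7675/0.715 = 1.073

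Over E from 0.20 to 0.40 and c from 0.80 down to 0.40, repairing half the shortfall takes the HR from 1.037 to 1.019 at the smallest and from 1.355 to 1.177 at the largest.

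In this model the excess HR − 1 shrinks by exactly the fraction r. If correction reaches only 10% of homes, r is at most about 0.10. It is lower still if part of the shortfall is missed redemptions or missed VHT visits, which checking placement does not repair. If every VHT home is corrected and most of the shortfall is poor placement, r could be 0.50 or more.

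**The case against.** The strongest reply is that only the VHT arm is shown to be affected. A reader might infer that staff correct placement in both operational arms and pull both HRs toward 1. The documents do not support that. The voucher section describes no staff check of hanging after the first month, and the objectives have households apply the product themselves. The re-engagement in {11c} is conditional and follows a sentence on product found to have been moved at a scheduled replacement. The reference-arm section ties staff work on prompt replacement to that arm, so {11c} can be read as mainly about it.

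Two further inferences are also too strong:
- That {16c} flatly contradicts the channel descriptions. It makes staff responsible for managing the process, which is compatible with VHTs or households carrying it out. The wording is loose.
- That correction happens every two weeks. Follow-up of the cohort lists what those visits ask about, and inspection of the SR is not among it. The 10% spot checks are described as monitoring.

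The article also expects the household application rate to be near 100%, which would leave little to repair. The trial is exploratory, makes no formal test, and expects an upper bound of about 1.30 even if the estimated HR is 1. An article may leave cost items to the full protocol. Moved product is recorded, and the per-protocol analysis may adjust for application and coverage.

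Most of this stands and limits the point. It does not remove the explicit sentence on the VHT arm. A wide interval does not excuse a systematic shift. An application rate near 100% is reassuring only if it is reached without staff help, which the article does not say. Adjusting for the achieved rate does not recover what the channel would have achieved unaided.

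**Conclusion.** The point holds for the VHT arm and is possible, but not shown, for the voucher arm. Correction by the study team is not part of the VHT channel as the objectives define it, and it may bias the VHT HR toward 1 and favour that channel in the cost-effectiveness comparison. The direction rests on one assumption: unaided VHT placement is worse than reference placement.

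The size cannot be derived from the article. It is negligible if correction is confined to a 10% sample (1.147 to 1.132 in the illustration) or if application is near 100% unaided. It is material if every VHT home is corrected (1.147 to 1.073 with half the shortfall repaired). This is an inexpensive improvement worth making, and does not by itself invalidate the comparison.

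**What to change.** Reword the VHT distribution channel section, {11c} and {16c} to say who checks, in which arms, how often, and whether problems are recorded or also corrected. Preferably:

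- In the VHT and voucher arms, study staff only observe and record placement, product count and replacement date.
- The same check, with the same sampling, is used in all three arms.
- Correction of placement is left to the channel's own actors: the VHT at the monthly visit, the distributor at redemption.
- Study-staff follow-up for safety and disposal stays in every arm.

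If staff correction is kept, log each correction by arm, include its cost in that channel, and describe the result as delivery under research supervision. The article expected enrolment in July and August 2024. If follow-up is under way, logging should start at once, because unlogged corrections cannot be separated from channel performance later.

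The cost is changed wording and matching procedures, with no extra staff or visits. The downside is somewhat lower coverage in the operational arms, which is what the trial is meant to measure.

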#### Study personnel distribution channel (reference arm)

In the reference arm, the SR products will be delivered and replaced by paid study personnel throughout the intervention period. The study personnel will distribute the SR every month during a data collection home visit. They will also retrieve used SR to ensure proper disposal of SR. Study personnel will track distribution and retrieval and follow-up on any discrepancies as needed to ensure safe product disposal.

CRS study staff will be employed to ensure proper storage of unused products at site and supply management and coordination for the timely replacement of products in the reference arm. The CRS study team will also perform periodic, unannounced spot checks in a random 10% of enrolled HHs during intervention to monitor SR product compliance (installation according to manufacturer specifications) and ITN usage, if available.

### Intervention description {11a}

The SR product used for the study will be a new formulation of transfluthrin, Mosquito Shield™, a passive emanator that releases active ingredient (AI) over a period of up to 4 weeks. SRs, like the Mosquito Shield™, are devices containing volatile chemicals that disperse in the air under ambient conditions (no requirement of electricity or heat to volatilize); they can be placed inside or around houses. The volatile chemicals introduced into the air repel mosquitoes from entering the treated space and/or disrupt human biting and feeding habits, possibly impacting their survival and reproductive behavior [12, 13]. SR products are envisioned to complement and enhance existing vector control methods due to the continual release of volatile AI which precludes the requirement of mosquito contact with a treated surface (i.e., ITN, IRS) providing: (1) protection against daytime, early-evening biting; (2) protection in enclosed/semi-enclosed and peri-domestic spaces; (3) a range of formulation options to fit context-specific application requirements thereby facilitating health systems strengthening; and (4) increase coverage of vector control over traditional methods. In addition, SR product AIs have demonstrated increased attraction to oviposition cues that could intervene in the vector life-cycle or enhance combination interventions (i.e., push–pull) that other interventions do not reach and have demonstrated an effect against insecticide-resistant vector species linked to malaria transmission [14, 15].

Transfluthrin is widely used in mosquito coils and other HH pest control products worldwide. The emanator consists of a pre-treated medium with a standard amount of transfluthrin that will be present throughout the treated space continuously based on a standardized 4-week replacement schedule. Products will be positioned along interior walls (approximately 2–3 m above ground) according to manufacturer specifications of 2 units per 9 m^2^. More than one emanator may be applied in a HH depending on the size of the house. The product will have a unique code associated with an individual distribution channel, which will be recorded at the time of installation and replacement.

### Criteria for discontinuing or modifying allocated interventions {11b}

If a study participant chooses to end their study participation, the study staff will respect the individual’s decision without penalty. Participants who withdraw from the study will still be eligible to receive care from government health facilities. If a study participant no longer meets the study’s inclusion criteria and/or based on AE and/or SAE clinical assessment, staff may terminate participant participation at any time during the study.

### Strategies to improve adherence to interventions {11c}

In order to promote adherence to intervention protocols, standard operating procedures will be developed for clinical tests, drug administration, distribution modalities, and all other study processes. Study staff will be employed and trained to ensure the timely replacement and accurate placement of the SR products. Additionally, they will perform periodic, unannounced spot checks to confirm the SR product is properly installed. If study staff observe a product has been moved after application during a scheduled product replacement, the move will be recorded for use in HH compliance assessment. If necessary, study staff will re-engage with heads of HHs on the importance of maintaining original product placement. Overall product coverage will be estimated based on total HHs recorded having product volume at time of replacement according to manufacturer specifications (2 units/9 m^2^).

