#### Voucher distribution channel

Trained study staff will confirm how many SR products are needed per structure. The voucher will be a small plastic card with a QR and/or barcode that is programmed with the total number of SR products that will be provided monthly to each head of the HH. The head of HH will retain the voucher.

For the initial month of the study, CRS staff will distribute the voucher and provide the SR during a HH visit along with training on product placement and handling. HH heads will be instructed where (central distribution location) and when (every month) they can redeem the SR product(s). For the remaining 11 months, HH heads will redeem their SRs. Vouchers will be redeemed at central distribution locations in the cluster, chosen by the voucher clusters’ community, for example, a health clinic, or food distribution point. Reminders to redeem their SR will be put in place for this distribution channel.

At the central distribution location, the distributor (trained as part of this study) will scan the voucher QR and/or barcode with an electronic device (e.g., tablet or smartphone). By scanning the voucher, the distributor will know and provide the exact number of SR product(s) to distribute to the HH head. The trained distributor will also request that heads of HHs return their old SR product to the central distribution location (for safe disposal) in exchange for the new ones. If there is a discrepancy in the number of returned SR products versus new ones to be issued, the distributors will still issue the total assigned number of new SRs. They will record reasons for the discrepancy. The CRS study Program Manager will then follow-up on these discrepancies to ensure safe product disposal according to the manufacturer’s instructions. If a HH size changes, the HH head will inform the central distribution location or CRS study personnel, which will kick-off a process by which CRS staff will check the new HH dimensions and re-issue a new QR code on a new voucher corresponding to the updated number of SRs to receive.

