#### Follow-up of the cohort

All efforts to overlay the commencement of enrollment with the start of the malaria transmission season will occur; however, programmatic timelines may not allow for perfect alignment. The 12-month follow-up period will ensure estimating potential changes in malaria incidence during anticipated seasonal malaria transmission peaks.

The distribution of the SR will occur after enrollment. At this time, cohort participants will be presumptively cleared of parasites with a treatment dose of AL unless they have recently been treated (within the last 2 weeks). This will be done so that the incidence of malaria infection following study product deployment can be measured.

Participants enrolled in the cohort will be followed every 2 weeks for malaria infection during the 12-month period after the study product has been distributed. All cohort participants and HH residents will also be informed to come to the nearest health facility for unscheduled sick visits, as needed. If the participant presents with a history of fever in the last 48 h, a RDT will be performed and AL will be administered if the RDT is positive for malaria.

Every 2 weeks, study team data collectors will visit the enrolled HHs. At each data collection HH visit, the parent/guardian will be asked about the recent use of ITNs and other vector control interventions as well as recent history of illness, recent travels outside the HH, and recent use of anti-malarial drugs.

During the first scheduled HH visit, a blood sample will be taken for malaria RDT (Monthly Visit #1). During the second scheduled HH visit, a blood sample will only be taken if the participant has a recent history of fever (Monthly Visit #2). The total blood volume for samples at each visit will not exceed 500 mli. A second blood sample may be taken for hemoglobin testing during follow-up only if the data collection/clinical team suspects anemia in participating children.

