#### Cost-effectiveness

We will address issues of cost of implementation by evaluating efficacy in relation to coverage using varied delivery systems. The cost of manufacturing the SR intervention by SCJ will be monitored and documented to model affordable pricing by industry stakeholders to produce next in class SR products ensuring efficacious options for procurement by donor agencies and countries. Projected cost per person protected will comprise product costs based on models using project data (epidemiological, and market) and operational costs. Treatment cost averted using ITNs vs ITNs + SR to the global scale is required for estimating the economic impact. The study will measure the cost of Mosquito Shield implementation in relation to manufacturing, efficacy, and coverage to model projections of cost-effectiveness to incentivize procurers.

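### Product coverage is counted at replacement, but in 11 of 12 voucher rounds replacement takes place away from the home, so coverage by channel may not be comparable

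*Protocol article*

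**What the plan says.** Strategies to improve adherence to interventions {11c} fixes the moment at which coverage is read: "Overall product coverage will be estimated based on total HHs recorded having product volume at time of replacement", against the manufacturer's density of 2 units per 9 m². Displaced product is tied to the same event: "If study staff observe a product has been moved after application during a scheduled product replacement, the move will be recorded". The section adds a source that does not depend on replacement: "they will perform periodic, unannounced spot checks to confirm the SR product is properly installed".

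The replacement event itself differs by arm:

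- **Reference.** "The study personnel will distribute the SR every month during a data collection home visit". Under this arm's heading, staff will also "perform periodic, unannounced spot checks in a random 10% of enrolled HHs during intervention to monitor SR product compliance".
- **VHT.** A trained VHT visits the home monthly, hands out and retrieves product, and keeps the tracking record. The same section has the study team check hanging, without saying when or how this is recorded.
- **Voucher.** Month 1 is a staff home visit with placement training. For the other 11 months, "Vouchers will be redeemed at central distribution locations in the cluster". The distributor issues the full allotment whatever is returned, and under Objectives {7} households put the product up themselves.

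Coverage has two later uses. The Cost-effectiveness section plans on "evaluating efficacy in relation to coverage using varied delivery systems". The additional analyses {20b} allow household application rate and cluster coverage rate as per-protocol covariates, on conditions that include meaningful variation in them.

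Follow-up of the cohort says "Every 2 weeks, study team data collectors will visit the enrolled HHs". The questions listed there cover ITNs and other vector control, illness, travel and antimalarials, but not the state of the repellent.

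**The concern.** The three channels differ by design in how product gets from store to wall. Coverage should describe how much product ends up on the wall. A rule that reads coverage at replacement works where replacement happens in the home. In the voucher arm it stops at the distribution point, so the step most likely to fail there, hanging by the household, lies outside what is recorded. A household that does not redeem has no replacement event at all, and the rule does not say how it counts.

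Two results could suffer. Cost-effectiveness by channel is the first secondary objective. If issue stands in for use in one arm and observed product is used in another, the cost comparison mixes two quantities. In the per-protocol models, application is expected to be close to 100%, and the covariates enter only if they vary meaningfully. Records based on issue could look nearly complete among redeemers, hide real variation in hanging, and lead to the covariate being dropped.

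**Working it through.** **1. Who can see the wall at replacement**

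| Arm | Replacement event | Recorder at that event | Product on the wall visible? |
|---|---|---|---|
| Reference | Monthly home visit | Study personnel | Yes |
| VHT | Monthly home visit | VHT, who also delivers | Yes, but self-reported; study-team check has no stated timing or record |
| Voucher, month 1 | Home visit | Study staff | Yes |
| Voucher, months 2–12 | Redemption at a distribution point | Distributor | No |

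Share of voucher rounds with no home observation at replacement: 11/12 = 0.917, or 92%. Returned units show possession, not that they had been hung.

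**2. Size of a possible overstatement (illustration)**

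The documents give neither a redemption rate nor a hanging rate. Let r be the share of voucher households that redeem and h the share of those that hang product to specification. Both are assumed, as is the reading that redemption counts as coverage.

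- Recorded coverage = r; in-home coverage = r × h; ratio = r/(r × h) = 1/h. The redemption rate cancels.

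| h | 1.0 | 0.9 | 0.8 | 0.7 | 0.6 |
|---|---|---|---|---|---|
| recorded / in-home | 1.00 | 1.11 | 1.25 | 1.43 | 1.67 |

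Example with r = 0.90: recorded coverage is 90%. In-home coverage is 0.90 × 0.8 = 72% or 0.90 × 0.6 = 54%, and 0.90/0.72 = 1.25, 0.90/0.54 = 1.67.

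If covered households were the cost denominator, the true cost per covered household would be 1/h times the reported one.

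**3. What the spot checks could supply**

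The plan's household total reproduces: 16 clusters × 45 households × 3 arms = 2,160, so 720 per arm. If the 10% applies equally to all arms and is read as one round, it gives 72 households per arm, or 72/16 = 4.5 per cluster.

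- Design effect = 1 + (4.5 − 1) × ICC.
- 95% half-width = 1.96 × √(p(1 − p) × design effect / 72).
- At p = 0.80 (assumed) and ICC 0: 1.96 × √(0.16/72) = 0.092.
- At p = 0.80 and ICC 0.10 (assumed): design effect 1.35, and 1.96 × √(0.16 × 1.35/72) = 0.107.

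One round would give a common in-home measure, accurate to about 9 to 11 percentage points per arm. That is usable but coarse, and it is not the stated basis of the coverage estimate.

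**4. Where coverage does not enter**

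The primary ITT model {20a} is specified with treatment group and baseline-type covariates, not coverage. The sample size does not depend on it either.

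**The case against.** A reader might infer that only the reference arm is observed. The documents do not support this. The adherence section provides for unannounced in-home spot checks in wording not limited to one arm. The VHT section has a study-team check of hanging, and voucher month 1 is a staff home visit. What remains is that the 10% sampling sentence sits under the reference-arm heading, so its scope is unclear.

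A reader might also infer that coverage means a different thing in each of the three arms. That goes too far. VHT replacement is a home visit, so the same quantity can be recorded there as in the reference arm; the weakness is that the recorder is also the deliverer. The real break is in the voucher arm.

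Third, the article never says that a redemption counts as coverage, and it refers to standard operating procedures for distribution. The full protocol or those procedures may define the observer and the form. This is fair, and it is why the size above is only an illustration. But the article does more than leave a detail open: it states a moment of measurement, and in the voucher arm that moment cannot show installed product.

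Finally, the costing is only outlined, and no formula divides cost by this coverage figure. That also stands.

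**Conclusion.** The point holds as a badly chosen measurement moment, chiefly for the voucher arm, where 92% of replacement rounds can document issue but not installation. In the VHT arm it is a lesser matter of self-recording. Coverage by channel may not be comparable.

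A firm conclusion that the cost-effectiveness result will be non-comparable is not supported; what follows is a risk of bias there and in the per-protocol covariates. The ITT hazard ratio is unaffected, and a real shortfall in hanging would already be reflected in it.

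The factor of 1.00 to 1.67 rests on assumed hanging rates of 100% down to 60% and on redemption being counted as coverage. Carrying it into cost also requires covered households to be the denominator. If every redeeming household hangs to specification, there is no overstatement. This is a worthwhile, inexpensive improvement, not a threat to the primary result.

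**What to change.** - In {11c}, define coverage, and moved or missing product, as units hung against units specified per structure. Study data collectors observe this at the existing two-weekly home visits, on one form in all three arms.
- Take the observation at the same point in the product cycle in every arm and before any replacement at that visit. The visit between replacements would also serve. This matters because reference-arm distribution takes place during a data collection visit, and a reading after it would show fresh product.
- Use this observed measure in the cost-effectiveness work and for the per-protocol covariates.
- Report issue, redemption and return logs separately as delivery-process measures, with non-redeeming households shown.
- State that the unannounced spot checks cover all three arms.
- Reconcile Implementation {16c}, which puts trained study staff in charge of removal and replacement without distinguishing arms, with the VHT and voucher sections.

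Cost: a few items on an existing tablet form, about a minute more per visit, and probably a lower stated coverage. No change to sample size or to the primary analysis.
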